# Early continuous ultrafiltration in Chinese patients with congestive heart failure (EUC-CHF): study protocol for an open-label registry-based prospective clinical trial

**DOI:** 10.1186/s12872-019-1208-y

**Published:** 2019-11-07

**Keywords:** Early ultrafiltration, Heart failure, Fluid overload, Loop diuretics, Continuous renal replacement therapy, Inflammatory cytokines

## Abstract

**Background:**

Conventional pharmacologic therapies aim to reduce fluid overload in advanced heart failure (HF) represented by intravenous (IV) loop diuretics (LDs) have sometimes not so efficacious and been reported to have side effects such as unpredictable removal of water and sodium and electrolyte disturbance. It is not certain whether early ultrafiltration (UF) is effective than LDs in relieving edema. Given the weakness of evidence for early UF in patients with fluid overload, recommendations of UF in guidelines is considered as second-line therapy only for patients with refractory congestion, who failed to respond to LD-based strategies.

**Methods:**

The early continuous ultrafiltration in Chinese patients with congestive heart failure (EUC-CHF) trial is an open-label, registry-based, prospective study, recruiting patients with severe acute decompensated HF who are hospitalized for HF worsening due to overt fluid overload 24 h from hospital admission. Forty patients will be enrolled to two treatment groups (*n* = 20 for each group). The primary outcomes are the changes of weight loss and dyspnea severity score after treatment, as well as the occurrence of clinically overt major bleeding.

**Discussion:**

EUC-CHF trial was primarily designed to evaluate the efficacy and safety of early UF in patients with acute decompensated HF to reduce volume overload and improve clinical outcome. The trial aims to determine if early UF in acute HF is superior to IV LDs in clinical parameter improvement without adverse events and prevents rehospitalization up to 30 days. Also the trial is expected to establish a scoring system based on Chinese population to guide early UF treatment in appropriate patients. EUC-CHF is one of the first controlled trials tailored to determine the benefit of UF with 24 h from hospital admission.

**Trial registration:**

www.chictr.org.cn, ChiCTR1800019556. Registered on 18 November 2018.

## Background

Fluid overload and congestion are major causes for hospitalization in advanced heart failure (HF). Therapies aim to reduce fluid overload are the most important targets of treatment for acute decompensated HF patients. Intravenous (IV) loop diuretics (LDs) are widely accepted as the initial treatment for fluid removal, and are recommended in the guidelines for most of the patients with acute HF admitted due to fluid overload to improve symptoms. However, inappropriate use of high dose LDs may induce hypovolemia, hypotension, activation of the neurohumoral axis, worsening renal function and electrolyte disturbances. Also, up to 30% of the patients with decompensated HF (NYHA classification III to IV) present with LDs resistance [1, 2]. So far, LDs have never been systematically validated as safe and efficacious in reducing long-term mortality of HF due to lack of randomized controlled large-scale studies. The side effects and lack of long-term benefits restrain its use.

Growing evidence from clinical research indicate that ultrafiltration (UF) is effective in relieving pulmonary and peripheral edema for patients with severe fluid overload and LD resistance, as well as ameliorating haemodynamics and restoring diuretic responsiveness. Treatment with UF may represent a more rapid and physiologic method of fluid removal than LDs therapy. It is associated with a better effect of decongestion and haemodynamic variables improvement as well as longer clinical stabilization and a lower rehospitalization rate compared with LDs [3–5].

Currently, UF recommend by most of the guidelines are usually considered for patients with refractory congestion not responding to medical therapy. Previous research found although UF improve hemodynamics in acute decompensated HF refractory to standard medical therapy, it was also associated with high incidence of renal function damage and high in-hospital mortality [6]. However, other research found UF within 12 h of hospitalization in HF patients with volume overload and LD resistance before IV LDs effectively decreased length of stay and readmissions up to 3 months without change of renal function [7]. At present, most of the studies support UF should be considered as early treatment strategies (24 h after admission) in patients with severe HF instead of a “rescue therapy”. Early UF may prevent undesirable cardiorenal syndrome and sodium-volume overload before renal tubular damage induced by further neurohormonal activation and side effects caused by high dose LDs [8, 9].

Taken together, previous related studies showed UF is more effective in decongestion, haemodynamic variables and clinical outcome improvement, as well as restoring LD responsiveness compared with LDs. But most of the studies were based on the foreign population and did not define the exact time period from admission to UF. We do not have the related data for early UF in Chinese population. Furthermore, former study did not define how to screen out the patients recommended for early UF by specific scoring system. Our study aims to determine if early UF 24 h within admission in acute HF is superior to IV LDs in clinical parameter improvement without adverse events and prevents rehospitalization up to 30 days in Chinese population.

## Methods/design

### Aim

The early continuous ultrafiltration in Chinese patients with congestive heart failure (EUC-CHF) trial was designed to evaluate the efficacy and safety of early UF in patients with acute decompensated HF to reduce volume overload and improve clinical outcome. In addition, the study will determine risk factors help to screen out patients appropriate for early UF treatment.

### Study overview

The EUC-CHF trial is an open-label, registry-based, prospective, single center study. It will recruit patients with severe acute decompensated HF who are hospitalized for HF worsening and significant weight gain due to overt fluid overload 24 h from hospital admission. The determination that acute decompensated HF is the primary cause of hospitalization will be made by the site’s principal investigator or sub-investigator, based on the assessment of the clinical signs and symptoms as well as laboratory examinations that lead to the admission. Patient enrollment should be completed and study treatment initiated within 24 h from hospital admission. Patients will be enrolled 1:1 sequentially to receive standard medical therapy (control group) or early UF (early UF group). Up to 2 doses of IV LDs will be allowed before enrollment.

The diuretic protocol adopted by our study in the control group refers to the protocol of AVOID-HF and CARRESS-HF trial as well as the dose recommended by the guideline according to patients’ vital signs, status of hemoconcentration, and renal function (Table 1) [10, 11]. Patients of the early UF group will be treated with a single or repeated session of UF within 24 h from admission (according to local clinical practice and with availability of nursing surveillance during UF) until the relief of patient’s symptom. The UF protocol adopted by our study also refer to the protocol of AVOID-HF and CARRESS-HF trial (Table 2).

[figure not shown]

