**1.** If satisfactory “dry weight” has been reached AND sCr is stable: **a.** Initiate oral loop diuretics with goal to keep net even (new dose of loop diuretics may be less than baseline dose in some patients) **b.** GDMT **2.** If sCr, hemodynamics, or UO are NOT stable: **a.** Hold diuretics until sCr is stable for minimum of 12 h, then: **i.** If “Dry Weight” /adequate decongestion has been reached then initiate oral diuretics as above **ii.** If “Dry Weight”/adequate decongestion has NOT been reached then initiate IV diuretics **b.** If elevated sCr or hemodynamic instability persist, then consider bolus of IV fluids	

Abbreviations: *BP* Blood Pressure, *BPM* Beats per Minute, *GDMT* Guidelines Directed Medical Therapy, *HR* Heart Rate, *IV* Intravenous, *LV* Left Ventricle, *RV* Right ventricle, *SBP* Systolic Blood Pressure, *sCr* Serum creatinine level, *UF* Ultrafiltration, *UO* Urine Output

During the process of UF, hematocrit will be monitored to reduce the risk of hypovolemia-induced acute kidney injury associated with excessive dehydration. In both group, protocol of inotropics and vasodilators use for each group are listed in Table 1 and 2. Other additional medical therapy will be left to the discretion of the cardiologist responsible for the patient. IV LDs started before enrollment will be discontinued during the process of UF. During the follow-up period, physicians can modify LDs dose according to patients’ situation according to the diuretic protocol.

UF will be performed with the FQ-16 HF UF dewatering device (HeartcareMedical Technology Co., Ltd., Beijing, China). Patients in the UF group will receive heparin to achieve an activated partial thromboplastin time (APTT) 1.5 to 2.5 times normal (or ACT180–220 s) or low molecular heparin according to routine clinical practice without monitoring APTT. The vascular access will be obtained by placing a double-lumen catheter (≥ 8 Fr) in a major venous vessel. The UF rate could be changed during the procedure according to the clinical situation (see in Table 2).

Key inclusion and exclusion criteria are shown in Table 3. The study design and schedule of follow-up visit are summarized in Fig. 1. EUC-CHF is registered at www.chictr.org.cn (ChiCTR1800019556). The trial started recruitment in December 2018 and enrolment of the first participant to the trial is on 14 December 2018.

**Table 3 Tab3:** Key inclusion and exclusion criteria of the study

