### Study outcomes

The primary end points of EUC-CHF are the changes of weight loss and dyspnea severity score at every scheduled visit which are considered as the part of a single composite endpoint, as well as the occurrence of clinically major bleeding defined by TIMI or GUSTO criteria [12].

Secondary outcomes include: net fluid loss, length of stay in CCU or ICU, change of score by MLWHFQ functional capacity, change of serum and ultrafiltrate concentrations of endotoxin, ET-1, TNF-a, IL-6 and IL-10, changes of cardiac function (the NYHA classification), changes in N-terminal proB-type natriuretic peptide (NT-proBNP) level, changes of LDs dose, HF rehospitalizations for congestive HF in 30 days after discharge, cardiovascular death and all-cause death in 30 days after discharge, change of blood pressure, changes in hepatic and renal function (serum creatinine concentration, estimated glomerular filtration rate [eGFR]), serum electrolytes, hemoglobin and incidence of acute coronary syndrome at scheduled visits.

Weights will be obtained at every scheduled visit using the same balance with the patient shoeless in a hospital gown after emptying the bladder. Weight loss is the difference between weight at baseline and the weight recorded at subsequent visits.

The dyspnea severity score by a proposal to standardize dyspnea measurement in clinical trials of acute heart failure syndromes by International Working Group on acute heart failure of European Society of Cardiology is used for the assessment of dyspnea [13].

Total fluid intake and output (ultrafiltrate and urine) measured at every scheduled visit after enrollment will be used to calculate net fluid losses.

Glomerular filtration rate will be calculated according to the abbreviated Modification of Diet in Renal Disease (MDRD) equation [14].

Acute coronary syndrome includes unstable angina, ST segment elevated myocardial infarction and non-ST segment elevated myocardial infarction. Myocardial infarction is defined according to the fourth universal definition of myocardial infarction [15]. Death will be considered cardiac according to the 2014 ACC/AHA key data elements and definitions for cardiovascular endpoint events in clinical trials [16].

We also will collect all the urine output after patients are enrolled to receive standard medical therapy or early UF until 72 h after the end of study treatment. Then we will measure the average urine electrolytes for every enrolled patient.

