### Statistical analysis

We will compare estimates of patients who receive UF therapy with those who receive conventional pharmacologic therapy. Concomitant medication and other baseline characteristics will be utilized in subgroup analysis.

Continuous variables will be summarized using descriptive statistics. Qualitative variables will be summarized by counts and percentages.

We will compare baseline characteristics. T-test or sign rank test will be used after testing for normality. Chi-square or Fisher’s exact test will be performed for categorical variables.

The primary efficacy endpoint (change of weight loss and dyspnea severity score) will be analyzed by Kaplan-Meier method, and comparisons between two groups will be performed using a log-rank test. Hazard ratio with 95% CI will be derived by the Cox proportional hazards model. Subgroup analyses of the efficacy endpoint are performed for the evaluation of impact of major clinical features on the improvement of primary efficacy endpoints by early UF therapy. Specific information is as follows:

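### Up to two IV loop diuretic doses may precede baseline in either arm, allocation is not described as random, and the stated primary comparison does not adjust for them

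*Protocol article*

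**What the plan says.** All places are in the protocol article.

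- **Question.** Background: "Our study aims to determine if early UF 24 h within admission in acute HF is superior to IV LDs in clinical parameter improvement".
- **Prior exposure.** Study overview: "Up to 2 doses of IV LDs will be allowed before enrollment". No arm is named. The time available for such doses is bounded: "Patient enrollment should be completed and study treatment initiated within 24 h from hospital admission".
- **What follows in each arm.** Control patients go on to loop diuretics as study treatment. For the UF arm, the text after Table 2 says: "IV LDs started before enrollment will be discontinued during the process of UF".
- **Allocation.** Study overview: "Patients will be enrolled 1:1 sequentially to receive standard medical therapy (control group) or early UF (early UF group". The trial is open-label and no random sequence or concealment is described, although two exclusion criteria in Table 3 mention randomization. The Discussion concedes that selection bias may be present.
- **Where the endpoints start.** Study outcomes: "Weight loss is the difference between weight at baseline and the weight recorded at subsequent visits". For the secondary fluid outcome: "Total fluid intake and output (ultrafiltrate and urine) measured at every scheduled visit after enrollment will be used to calculate net fluid losses". Baseline weight and dyspnea score are taken at the visit where consent is obtained (text after Fig. 1). Drugs used in the three months before enrollment are recorded at the same visit.
- **Analysis.** Statistical analysis gives Kaplan-Meier curves, a log-rank test and a Cox hazard ratio for the primary efficacy endpoint, with no covariate named. On medication it says: "Concomitant medication and other baseline characteristics will be utilized in subgroup analysis".

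**The concern.** The pre-enrollment doses belong to the same drug class as the comparator, and the clock for the primary efficacy endpoint most likely starts after them. In a concealed randomized trial the number of such doses would balance in expectation, and the allowance would only affect how the question is worded. Here nothing described protects that balance: allocation is open and sequential, and if the next arm can be foreseen, early dosing could depend on it.

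A difference in prior doses would move the weight and dyspnea comparison without any difference between the study treatments. The stated log-rank and Cox comparison would carry that shift straight into the primary result. The planned subgroup analyses ask which patients respond to UF. They do not remove an arm difference in a pre-treatment factor.

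**Working it through.** **Plan's own figure.** The article gives 40 patients (20 per group) with no effect size, SD or power, so there is no calculation to reproduce.

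**Inputs from the article.** 0 to 2 prior doses per patient; 20 per group; two-sided 5% level.

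**Assumed inputs, because the article gives none.** Let *c* be the net change in weight loss after baseline per prior dose, in kg, taken as linear and equal in the two arms. It combines two opposing parts: residual diuresis after baseline adds to the loss, and fluid already removed before baseline may leave less to lose. Its sign is therefore unknown. I take its size as 0.2, 0.5 or 1.0 kg.

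**Step 1: bias.** If loss after baseline = treatment effect + *c* × doses, then

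bias in (UF − control) = *c* × (mean doses in UF − mean doses in control).

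| Size of *c* (kg per dose) | Equal mean doses | 0.5 dose apart | 1 dose apart | 2 doses apart (ceiling) |
|---|---|---|---|---|
| 0.2 | 0 | 0.10 kg | 0.20 kg | 0.40 kg |
| 0.5 | 0 | 0.25 kg | 0.50 kg | 1.00 kg |
| 1.0 | 0 | 0.50 kg | 1.00 kg | 2.00 kg |

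**Step 2: direction.**

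| | More prior doses in control | More prior doses in UF |
|---|---|---|
| Residual diuresis dominates (*c* > 0) | favours control | favours UF |
| Earlier loss dominates (*c* < 0) | favours UF | favours control |

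The article fixes neither the row nor the column.

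**Step 3: imbalance from chance alone.** Suppose doses are spread evenly over 0, 1 and 2 (assumption). The SD is √(2/3) = 0.816. The standard error of the difference in means is 0.816 × √(2/20) = 0.258, and the 95% range is ±1.96 × 0.258 = ±0.51 dose. Half a dose is thus near the edge of what chance gives with 20 per arm. Non-random allocation could exceed it.

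**Step 4: scale.** By the normal approximation, 20 per group detects (1.960 + 0.842) × √(2/20) = 0.886 SD at 80% power. At an assumed weight-loss SD of 2 to 3 kg that is 1.77 to 2.66 kg. With *c* = 0.5 kg:

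- 0.5 dose apart: 0.25/1.77 = 14% down to 0.25/2.66 = 9% of the detectable difference.
- 1 dose apart: 0.50/1.77 = 28% down to 0.50/2.66 = 19%.

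This uses a difference in means for scale only. The planned method is time-to-event and the article gives no event definition, so a shift in kg cannot be turned into a hazard ratio. For the dyspnea score there is not even a basis for an assumed effect per dose, but the same structure applies.

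**The case against.** **The allowance is common to both arms.** This stands. Any response before baseline is left out of both arms, and any residual diuresis is counted in both. A reader might infer that control loses its early response while UF is credited with the carry-over, so that the error favours UF. The documents do not support this. The two effects act in opposite directions, and for carry-over to favour UF the UF arm must have had more prior doses, not fewer. Nothing in the article says that the arm is known when these doses are given or that clinicians hold diuretics for patients due for UF.

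**A false-positive rate cannot be attached to the plan.** This also stands. A two-sample t test with 20 per arm, an assumed shift of 0.15 to 0.8 kg and an assumed SD of 2 to 3 kg gives 5.3% to 23% in place of 5%. A reader might quote that range as the trial's error rate. Every input is assumed, it treats prior doses as a shift in one known direction, and the t test is not the planned primary analysis.

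**Baseline at enrollment is conventional.** Agreed. The question becomes UF versus continued loop diuretics after at most two doses, which is an interpretation and not an error.

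**Covariates belong in the SAP.** This stands in part. The SAP is not shown, and if it already adjusts for prior doses the point is closed. But the article does not leave the matter silent: it states a primary comparison without covariates and says what medication data are for, namely subgroups.

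**The root problem is allocation.** True, and adjusting for one factor does not repair it. This factor is singled out because it is prior exposure to the comparator's own drug class and should be recoverable from data the trial already plans to record.

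**Conclusion.** The point holds in a limited form, at low severity. Prior IV loop diuretic doses can differ between arms, and the stated primary comparison would not correct for it. On the linear model the bias is zero if mean doses are equal. At half a dose apart it is 0.10 to 0.50 kg for an assumed net effect of 0.2 to 1.0 kg per dose, in a direction that cannot be given in advance.

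This rests on three things that the article does not state: that the baseline weight and dyspnea score follow the prior doses (the natural reading, since consent is taken at that visit), that the net effect per dose is linear and the same in both arms, and the size of that effect. No claim that the plan favours UF is warranted.

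**What to change.** In Statistical analysis, state that the between-arm comparison of weight loss and dyspnea change is adjusted for the number (0, 1 or 2) of IV loop diuretic doses given before enrollment, for example as a single linear term in the Cox model already planned. Report that number by arm with the other baseline characteristics. Take it from the pre-enrollment drug record made at the baseline visit.

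The cost is one degree of freedom among 40 patients. The drug record must also capture the count of IV doses, since the article promises a record of drugs used but does not mention a dose count. Stating whether baseline weight is taken after the last such dose would settle the inference above.

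A sensitivity analysis from an admission weight is worth running only where such a weight happens to exist, because none is scheduled. Net fluid loss is a secondary outcome planned as summary statistics, so showing the dose count beside it is enough. None of this alters the allowance or any treatment rule.

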**Table 1 Tab1:**
[figure not shown]
Treatment guidelines for the control group

Abbreviations: *BID* Twice daily, *BP* Blood Pressure, *BPM* Beats per Minute, *EF* Ejection Fraction, *GDMT* Guidelines Determined Medical Therapy, *HCT* Hematocrit, *HR* Heart Rate, *IV* Intravenous, *QD* Once daily, *RV* Right ventricle, *SBP* Systolic Blood Pressure, *sCr* Serum creatinine level, *UO* Urine Output

**Table 2 Tab2:** Treatment guidelines for the early UF group

General Comments:	
**1.** Once an initial UF rate is chosen, avoid increasing the UF rate unless there are clear indications to do so. **2.** Because patients’ plasma refill rate usually declines as fluid is removed, it should be expected that UF rate will need to be decreased during the course of therapy. **3. a** IV inotropes if SBP < 110 mmHg and EF < 40% or RV systolic dysfunction. **b** Nitroglycerin or Nesiritide if SBP > 120 mmHg (any EF) and Severe Symptoms	
A. Choose Initial UF Rate:	
SBP < 100 mmHg: 150 cc/hr. SBP 100-120 mmHg: 200 cc/hr. SBP > 120 mmHg: 250 cc/hr	
B. Decrease starting UF rate by 50 cc/hr if any of the following are present:	
**a.** RV > LV systolic dysfunction **b.** sCr increase 0.3 mg/dl above recent baseline **c.** Baseline sCr > 2.0 mg/dl **d.** History of instability with diuresis or UF in the past	
C. Re-evaluate UF rate every 6 h:	
**1.** Evaluate recent BP, HR, UO, sCr, HCT, Net intake/output **2.** Consider decreasing UF rate by 50 cc/hr. and checking STAT sCr (unless sent in past 2 h) if: **a.** sCr rise > 15% or > 0.2 mg/dl (whichever is less) compared to prior measurement **b.** HCT rises by > 5% compared to prior measurement **c.** resting SBP decreases > 10 mmHg compared to prior 6 h, but remains > 80 mmHg **d.** UO drops > 50% compared to prior 6 h, but remains > 125 cc/6 h **e.** resting HR increases by > 20 bpm compared to prior 6 h, but remains < 120 bpm **3.** Strongly consider holding UF and checking STAT sCr if: **a.** sCr rise by > 30% or > 0.4 mg/dl (whichever is less) compared to prior measurement **b.** HCT rises by > 10% compared to prior measurement **c.** resting SBP decreases > 20 mmHg compared to prior 6 h or is < 80 mmHg **d.** UO < 125 cc/6 h **e.** resting HR increases by 30 bpm compared to prior 6 h or is > 120 bpm **4.** If UF held, re-evaluate after laboratory values are available: **a.** If hemodynamics is stable and sCr has plateaued, then consider re-starting UF at rate 50-100 cc/hr. less than previous rate **b.** If persistent volume overload is present, then consider: **i.** Adjusting doses of IV inotropes in patients with LVEF < 40% or RV systolic dysfunction **ii.** Weaning venodilators, especially in patients with HFpEF **iii.** Right heart catheterization	
D. Consider completion of UF therapy If ONE of the following occurs:	
**1.** Resolution of congestion (all of following): **a.** Jugular venous pressure < 8 cm H_2_O **b.** No orthopnea **c.** Trace or no peripheral edema **2.** Best Achievable “Dry Weight” has been reached **a.** Evidence of poor tolerance of fluid removal AND **b.** UF rate < 100 cc/hr. or net negative < 1 l/24 h **3.** Persistent elevation in sCr > 1.0 mg/dl above baseline at start of UF treatment **4.** Persistent hemodynamic instability	
E. After completion of UF Therapy:	
**1.** If satisfactory “dry weight” has been reached AND sCr is stable: **a.** Initiate oral loop diuretics with goal to keep net even (new dose of loop diuretics may be less than baseline dose in some patients) **b.** GDMT **2.** If sCr, hemodynamics, or UO are NOT stable: **a.** Hold diuretics until sCr is stable for minimum of 12 h, then: **i.** If “Dry Weight” /adequate decongestion has been reached then initiate oral diuretics as above **ii.** If “Dry Weight”/adequate decongestion has NOT been reached then initiate IV diuretics **b.** If elevated sCr or hemodynamic instability persist, then consider bolus of IV fluids	

Abbreviations: *BP* Blood Pressure, *BPM* Beats per Minute, *GDMT* Guidelines Directed Medical Therapy, *HR* Heart Rate, *IV* Intravenous, *LV* Left Ventricle, *RV* Right ventricle, *SBP* Systolic Blood Pressure, *sCr* Serum creatinine level, *UF* Ultrafiltration, *UO* Urine Output

During the process of UF, hematocrit will be monitored to reduce the risk of hypovolemia-induced acute kidney injury associated with excessive dehydration. In both group, protocol of inotropics and vasodilators use for each group are listed in Table 1 and 2. Other additional medical therapy will be left to the discretion of the cardiologist responsible for the patient. IV LDs started before enrollment will be discontinued during the process of UF. During the follow-up period, physicians can modify LDs dose according to patients’ situation according to the diuretic protocol.

UF will be performed with the FQ-16 HF UF dewatering device (HeartcareMedical Technology Co., Ltd., Beijing, China). Patients in the UF group will receive heparin to achieve an activated partial thromboplastin time (APTT) 1.5 to 2.5 times normal (or ACT180–220 s) or low molecular heparin according to routine clinical practice without monitoring APTT. The vascular access will be obtained by placing a double-lumen catheter (≥ 8 Fr) in a major venous vessel. The UF rate could be changed during the procedure according to the clinical situation (see in Table 2).

Key inclusion and exclusion criteria are shown in Table 3. The study design and schedule of follow-up visit are summarized in Fig. 1. EUC-CHF is registered at www.chictr.org.cn (ChiCTR1800019556). The trial started recruitment in December 2018 and enrolment of the first participant to the trial is on 14 December 2018.

**Table 3 Tab3:** Key inclusion and exclusion criteria of the study

Inclusion criteria	1. Patient must be more than 18 years old. 2. Acute decompensated HF within 24 h of hospital admission. 3. Fluid overload, defined as edema of the lower extremities and at least 1 of the following: 1) elevated jugular venous pressure > 10 cm H_2_O, 2) pulmonary rales, paroxysmal nocturnal dyspnea or orthopnea, 3) pulmonary edema or pleural effusion on chest X-ray, 4) enlarged liver or ascites, 5) pulmonary wedge or left ventricular end diastolic pressure ≥ 20 mmHg, or 6) rapid increase of body weight ≥ 2 kg. 4. NYHA classification III-IV. 5. Patient is informed and has signed informed consent. Patient is willing to attend an outpatient follow-up.
Exclusion criteria	1. Acute coronary syndrome. 2. Severe mitral or aortic stenosis. 3. Severe renal insufficiency (serum creatinine ≥3.0 mg/dl or eGFR ≤ 30 mL/min). 4. Systolic blood pressure ≤ 90 mmHg or depending on high dose of vasoactive drug to maintain systolic blood pressure ≥ 90 mmHg. 5. Hematocrit > 45%. 6. Unattainable venous access. 7. Comorbidities expected to prolong hospitalization. 8. Contraindications to anticoagulation. 9. Serious bleeding in the last 6 months (this includes, but is not limited to, prior intracranial hemorrhage, active peptic ulcer disease, active internal bleeding, bleeding at a noncompressible site). 10. Hematuria within 30 days before randomization. 11. Patients at high risk of bleeding (this includes, but is not limited to, clinically significant thrombocytopenia or anemia, platelet count < 90,000/μL at screening or pre-randomization, anemia of unknown cause with a hemoglobin level < 10 g/dL at screening or pre-randomization, coagulation disorders, recent stroke within past 30 days, documented hemorrhagic tendencies, or blood dyscrasias). 12. Uncontrolled hypertension (> 180/110 mmHg). 13. Severe infection. 14. Use of iodinated radiocontrast material. 15. Participation in another controlled clinical trial, either within the past 2 months or still ongoing. 16. Women who are pregnant, breast-feeding, or of child-bearing potential. 17. Patient who is mentally ill.

